##### Hypotheses testing

Given the developmental nature of this study, our primary goal is to establish feasibility and acceptability of the LS-DU and assessment procedures to be implemented in a future larger scale hybrid type 2 randomized trial. Our primary hypothesis is that participants completing and community clinicians delivering the LS-DU intervention will report high levels of acceptability of the intervention. Our secondary hypothesis is that the LS-DU intervention will demonstrate greater effectiveness than the health education outcome in terms of promoting days of adherence to HIV medication and reducing substance use. We will also collect exploratory data on implementation potential of the intervention and moderators of implementation effectiveness. Due to the small sample size, we will primarily be hoping to find a pattern of results that is supportive of the LS-DU rather than rigorously testing hypotheses to determine a stable effect size.

##### Primary outcomes: acceptability

Participants’ mean ratings of the program satisfaction questionnaire will be examined to determine level of satisfaction of the LS-DU.

##### Feasibility

We will monitor the feasibility of the pilot trial by tracking recruitment, retention, and adherence rates of participants. We will assess feasibility of the intervention through qualitative interviews with the clinicians and a subset of patients.

##### Effectiveness

We will measure treatment effectiveness via adherence to HIV medication (MEMScaps), viral load (eligibility screener vs. baseline vs. 6-months), and days of drug use (Timeline Followback). Separate Generalized Estimating Equation (GEE) models for adherence will be generated for proportion of days on which study medication was taken (as indicated by MEMScap) and the proportion of expected pills taken at the 1-, 3-, and 6-month follow-ups. Examining interactions between intervention and time will test differences in adherence over the course of the intervention across the intervention conditions. As our sample size limits our ability to conduct sophisticated longitudinal analyses, we will use GEE with caution and will revert to more standard general linear models should we encounter model convergence problems. Additional measures of treatment effectiveness, including self-reported adherence, viral load, and drug use, will also be analyzed using GEE.

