### Phase 3 procedures: type 1 hybrid effectiveness-implementation pilot trial

#### Overview

Following the open trial, a pilot type 1 hybrid randomized effectiveness-implementation trial will be conducted to determine the effectiveness of the LS-DU protocol relative to health education. Hybrid effectiveness-implementation trials are designs that simultaneously gather data on treatment effectiveness and implementation outcomes [19]. In a type 1 hybrid trial, the primary emphasis is on the evaluation of treatment effectiveness, and the secondary emphasis is on the collection of data on implementation outcomes. Because the current study is designed to collect pilot data for a future study, measures of acceptability and feasibility are defined as the primary outcomes. Measures of effectiveness are then defined as the secondary outcomes, while data on implementation effectiveness are gathered as an exploratory outcome.

All participants will complete a baseline assessment consisting of a series of self-report measures and a urine toxicology screen. Following completion of the baseline assessment, participants will begin 2 weeks of baseline ART adherence data collection using an electronic pill cap monitoring system (MEMScaps). Only after completing the MEMS data collection will patients be randomly assigned to treatment condition using urn randomization [20] controlling for gender and viral load.

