#### Treatment conditions

Participants will be randomized to either the LS-DU experimental intervention or the health education control. We considered using the original Life Steps as a comparator condition; however, we believe that a minimally active, but ethical control group is the most direct test of the intervention (relative to treatment as usual). A more active control intervention, such as the original Life Steps protocol, may attenuate potential effects and would require a much larger sample size. The LS-DU intervention will utilize the manual refined at the end of Phase 2. Health education is a time-matched control condition that covers a variety of general health topics and has proven to be a credible control condition in prior studies [21]. Intervention clinicians will be given a health education training manual and will complete videotaped role plays. Two independent coders will assess fidelity to the health education intervention using a topic checklist. Both conditions will consist of two in-person intervention sessions of 60 min duration separated by 1 week. The LS-DU intervention will also consist of two follow-up booster phone sessions at 1 and 2 months following the last in-person session.

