#### Quantitative data analysis plan

Considering this is a pilot project, analyses will have the goal of establishing feasibility and estimation of effect sizes, with modest expectations for rejection of the null hypotheses. As a first step, the equivalence of treatment condition assignment with regard to key baseline variables will be assessed on demographic characteristics, baseline ART adherence measures (self-report and viral load), drug category and addiction severity, and baseline levels of potential treatment mechanisms and moderators using tests of proportions or t-tests as appropriate. Should conditions differ on any characteristic; these variables will be used as covariates in outcome analyses. Other preliminary analyses will include patterns of missing data, research dropout rates, distributional properties of dependent and other measures, and correlations among outcome measures.

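### Baseline MEMS adherence is collected before randomisation but has no assured place in the adherence models, at a cost in precision and in protection against adherence-related dropout

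*Protocol article*

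**What the plan says.** All references are to the Protocol article.

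- **Model (Effectiveness).** "Separate Generalized Estimating Equation (GEE) models for adherence will be generated" for two MEMS outcomes: the proportion of days with medication taken and "the proportion of expected pills taken at the 1-, 3-, and 6-month follow-ups". "Examining interactions between intervention and time will test differences in adherence" between arms. If the GEE fails, the team "will revert to more standard general linear models should we encounter model convergence problems". No covariates, weights or working correlation are named.
- **Covariate rule (Quantitative data analysis plan).** The arms are compared at baseline, and a variable becomes a covariate only if they differ on it. The adherence entry in that comparison reads "baseline ART adherence measures (self-report and viral load"; MEMS is not mentioned.
- **Missing data (same section).** "Other preliminary analyses will include patterns of missing data, research dropout rates". These are listed as preliminary checks.
- **Baseline MEMS (Phase 3 Overview; Table 3).** After the baseline assessment, "participants will begin 2 weeks of baseline ART adherence data collection using an electronic pill cap monitoring system (MEMScaps", and randomisation follows only when that is complete. The urn scheme controls for gender and viral load, not MEMS.
- **Contact by arm (Treatment conditions).** "The LS-DU intervention will also consist of two follow-up booster phone sessions at 1 and 2 months". No such calls are described for the control arm.

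**The concern.** Baseline MEMS is measured on the same device as the outcome, before assignment, in everyone randomised. It is likely to be the best single predictor of later MEMS adherence. As written, it enters the model only if it is counted among the variables tested for balance and then happens to differ by arm.

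Two things are at stake. The first is precision. The Participants section makes a reasonable effect-size estimate the main objective of Phase 3, and 30 per arm leaves that estimate imprecise. The second is dropout. A GEE fitted without weights or imputation is consistent only if missingness is unrelated to the outcome given the covariates in the model. A strong predictor of adherence that is left out cannot help to meet that condition. If poorly adherent controls were lost more often than poorly adherent LS-DU patients, the remaining controls would look better and the LS-DU effect would be understated.

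**Working it through.** **1. The plan's own figures.** The article gives no dropout rate, correlation or standard error for adherence. The nearest figures are the power values in Participants. With 30 per arm and outcome SD 1, the unadjusted SE is √(2/30) = 0.258. At one-sided 5% (not stated in the article), d = .60 gives Φ(0.60/0.258 − 1.645) = .75. For d = .65 the result is .81 by the normal and .80 by the t distribution. These match the stated .75 and .80, so those two figures fit an unadjusted comparison with this SE. The stated .54 at d = .40 does not reproduce (.46). That is a separate matter on which nothing here rests.

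**2. Precision.** Adjusting for a baseline value with correlation ρ to the outcome multiplies the variance by 1 − ρ². This is a linear-scale approximation that ignores the small loss of degrees of freedom.

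| Assumed ρ | 1 − ρ² | SE, 30 per arm | Equivalent unadjusted n per arm |
|---|---|---|---|
| none | 1.00 | 0.258 | 30 |
| 0.5 | 0.75 | 0.258 × √0.75 = 0.224 | 30/0.75 = 40 |
| 0.7 | 0.51 | 0.258 × √0.51 = 0.184 | 30/0.51 = 59 |

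If correlation decays by visit at 0.7 per step, the 6-month value is 0.7³ = 0.34 and the variance cut at that visit is only 0.34² = 12%.

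**3. Would the covariate rule bring it in anyway?** Suppose MEMS were included in the balance check and tested at 5% (assumed). Under randomisation the test would be positive in about one trial in 20, so the variable would usually stay out.

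**4. If baseline were modelled as a further time point.** The arm-by-time contrast would then compare changes from baseline, with variance factor 2(1 − ρ). That is 1.00 at ρ = 0.5 (no gain) and 0.60 at ρ = 0.7, against 0.75 and 0.51 with baseline as a covariate.

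**5. Exposure to dropout.** Large-sample simulation: 100,000 per arm, normal outcome, true effect 0.50 SD at each visit, correlation 0.5–0.7 (compound symmetric or AR(1)), monotone logistic dropout depending on baseline or on the last observed adherence. All of these are assumptions. Bias at 6 months, GEE without baseline:

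| Dropout scenario | Independence | Exchangeable |
|---|---|---|
| Unrelated to adherence, 15% v 30% | about 0 | about 0 |
| Same slope, 25% in each arm | about 0 (at most 0.02) | about 0 (at most 0.02) |
| Same slope, control 30% v LS-DU 15% | −0.06 to −0.10 | −0.02 to −0.05 |
| Adherence-driven in controls only, 25% each | −0.08 to −0.17 | −0.02 to −0.08 |

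Only opposite slopes in the two arms, or 40% loss driven by adherence in controls alone, took the independence fit well beyond this (to −0.34 at most).

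**6. What baseline adjustment recovers.** In the scenarios where the slope differs by arm, an independence fit with a baseline term for each visit removed:
- 97–99% of the bias when dropout depended on baseline;
- 62–79% when it depended on last observed adherence, compound symmetry;
- 44–56% when it depended on last observed adherence, AR(1).

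A single baseline slope common to all visits can overcorrect: in one AR(1) case the exchangeable fit moved from −0.023 to +0.050. Retention weights built from baseline and last adherence left at most 0.014.

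**The case against.** The strongest reply is that this is a condensed journal article. A reader might infer that the trial will run an unweighted GEE on whoever attends, and that its adherence estimate will therefore be biased. The article says neither. It names no weights, imputation or working correlation, and such details are commonly left to a full protocol or analysis plan. Its silence is not an error. Nor does it give any dropout figure. Booster calls in one arm and compensation offered to participants generally do not show that loss will be adherence-driven and different between arms. This part of the reply stands, so step 5 is conditional throughout.

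It is also fair that effectiveness is a secondary outcome, that Hypotheses testing looks for a supportive pattern and not a stable effect size, and that the moderate-scenario bias is well below one SE (0.26 SD, or √(2/22.5) = 0.30 SD after 25% loss). The simulations use normal outcomes and very large samples, so they do not show that a mixed model or imputation would do better with 60 patients and bounded proportions. Replacing the GEE is therefore not supported.

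What the reply does not reach is the covariate rule, which is stated. Admission depends on an imbalance, and MEMS is not on the named list. Effect-size estimation is given as a goal in both Participants and the Quantitative data analysis plan, so a precision gain from data already in hand is relevant.

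**Conclusion.** The point holds as a matter of baseline adjustment. The stated rule gives pre-randomisation MEMS no assured place in the adherence models. The cost in precision is an SE of about 0.26 SD instead of 0.18–0.22 SD with 30 per arm, if the baseline-to-follow-up correlation is 0.5–0.7; the gain is smaller if correlation decays over visits.

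The dropout argument is secondary and conditional. At an assumed 30% v 15% dropout the bias is about −0.02 to −0.10 SD, and it is near zero when the arms share the same mechanism and rate. On a true 0.50 SD, that range would inflate a later trial's required sample size by (0.50/0.48)² − 1 = 9% to (0.50/0.40)² − 1 = 56%.

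A reader might also infer that baseline MEMS would remove most of any such bias. That is not generally so: when dropout follows post-randomisation adherence and correlation decays, it removes only about half.

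**What to change.** - Prespecify baseline MEMS adherence, with its interaction with visit, as a covariate in both adherence models, whatever any balance test shows. Carry it into the general linear model used as fallback.
- State the working correlation and the missing-data assumption alongside the GEE.
- Keep the GEE as the main analysis. Add one sensitivity analysis valid under missing at random that uses earlier adherence: multiple imputation, retention weights or a mixed model.
- Participants promises odds ratios for adherence. If a logit link is used, say that the adjusted odds ratio is conditional on baseline, or standardise it to a marginal effect.

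The cost is a little more analysis work; no new data are needed. The sensitivity analysis brings its own modelling assumptions, which at this sample size is why it should support the main analysis and not replace it.

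### For MEMS adherence the named test is intervention-by-time, which on the plain reading tests whether the arm difference changes after month 1, not whether LS-DU gives better adherence

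*Protocol article*

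**What the plan says.** The Effectiveness section plans separate GEE models for two MEMS measures: the proportion of days with medication taken, and "the proportion of expected pills taken at the 1-, 3-, and 6-month follow-ups". The only test it names for these models is: "Examining interactions between intervention and time will test differences in adherence over the course of the intervention across the intervention conditions". It names neither an averaged arm effect nor an arm difference at a chosen visit. If the GEE fails, the authors "will revert to more standard general linear models should we encounter model convergence problems".

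Other sections bear on this:

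- **Hypotheses testing:** for effectiveness, the authors expect the following: "the LS-DU intervention will demonstrate greater effectiveness than the health education outcome in terms of promoting days of adherence to HIV medication". This is a difference between arms.
- **Participants:** the power statement is for the difference between two groups of 30. Odds ratios are promised as the adherence effect size.
- **Phase 3 Overview and Table 3:** MEMS adherence is recorded for two weeks before randomisation and again at all three follow-ups.
- **Quantitative data analysis plan:** baseline variables enter the outcome models only on condition: "Should conditions differ on any characteristic; these variables will be used as covariates in outcome analyses". The baseline adherence measures listed there are self-report and viral load, not MEMS.
- **Treatment conditions:** "Both conditions will consist of two in-person intervention sessions of 60 min duration separated by 1 week". LS-DU adds telephone boosters one and two months after the last session.

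**The concern.** The in-person treatment is delivered within about a week, so a plausible good result is an adherence gain visible by month 1 and kept through month 6. An interaction confined to the follow-up visits gives no credit for that pattern, because it compares the arm difference at one follow-up with the arm difference at another. If the benefit fades, the same test may become significant, and a reader could take a sign of lost benefit for evidence of efficacy. At stake is whether the one test stated for adherence answers the hypothesis stated for adherence, and whether the contrast that a larger trial would plan on is the one put forward.

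**Working it through.** **Inputs from the protocol article.** 30 per arm and d from .40 to .60 (Participants); follow-ups at 1, 3 and 6 months (Effectiveness); baseline MEMS collected (Phase 3 Overview, Table 3).

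**Assumptions, not in the document.** Two-sided alpha .05; the same within-person correlation ρ between any two visits, shown for .3 to .7; unit variance; no dropout; normal-theory Wald tests as an approximation for the proportions.

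**The plan's own figure.** Participants gives power .54 to .75 for d = .40 to .60, and .80 above d = .65. A two-group comparison of 30 per arm at one-sided .05 gives .75 at d = .60 and .81 at d = .65, but .46 at d = .40 (.54 corresponds to d = .45). At two-sided .05 the values at .40, .60 and .65 are .34, .64 and .71. The low end is therefore not reproduced, which is a separate matter. What counts here is that the stated power is for a difference between arms, not for an interaction.

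**Step 1: time = months 1, 3, 6.** Let δ1, δ3, δ6 be the arm differences. The interaction tests δ3 − δ1 = 0 and δ6 − δ1 = 0. If δ1 = δ3 = δ6 = d, both contrasts are zero, the noncentrality is 0, and power = alpha = .05 for every d and every ρ.

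**Step 2: arm difference averaged over the three follow-ups.** Variance of a person's mean = (1 + 2ρ)/3. At ρ = .6 this is 2.2/3 = .733. z = .6/√(2 × .733/30) = 2.71; power = Φ(2.71 − 1.96) = .77.

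**Step 3: the same average, adjusted for baseline.** Variance = (1 + 2ρ)/3 − ρ² = .733 − .36 = .373. z = .6/√(2 × .373/30) = 3.80; power = Φ(3.80 − 1.96) = .97.

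**Step 4: interaction with baseline as a fourth time level.** With no difference at baseline and d at each follow-up, the 3-df noncentrality is n·d²·(3/4)/[2(1 − ρ)] = 30 × .36 × .75/.8 = 10.1; power = .77.

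| d | ρ | Interaction, follow-ups only | Interaction, baseline as a level | Average | Average, baseline-adjusted |
|---|---|---|---|---|---|
| .4 | .3 | .050 | .239 | .564 | .643 |
| .4 | .5 | .050 | .325 | .475 | .670 |
| .4 | .7 | .050 | .518 | .410 | .795 |
| .6 | .3 | .050 | .502 | .889 | .937 |
| .6 | .5 | .050 | .660 | .812 | .949 |
| .6 | .6 | .050 | .767 | .774 | .967 |
| .6 | .7 | .050 | .884 | .738 | .987 |

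The baseline-adjusted average has the highest power in every row. The unadjusted average does not always beat the interaction that includes baseline: at ρ = .7 it is lower.

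**Step 5: simulated check.** A Gaussian GEE (exchangeable working correlation, robust variance, 600 runs, d = .65, ρ = .5) rejected in 5.7% of runs for the follow-up interaction, 89% for the arm effect and 77% for the interaction including baseline.

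**Step 6: fading benefit.** With differences .6, .3, 0 and ρ = .5, the follow-up interaction has power .54 and the averaged effect .30. A significant interaction here means that the benefit is being lost.

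**The case against.** The strongest reply is that the text does not exclude baseline. Baseline MEMS exists, Table 3 lists it, viral load in the same paragraph is compared with baseline, and a test over the course of the intervention can be read as a trajectory starting there. On that reading arm-by-time is a recognised test of effect, and Step 4 shows that it has power. This stands as far as it goes: the insensitivity in Step 1 depends on baseline not being a time level. But the adherence sentence names only the follow-ups, and the baseline rule elsewhere is a conditional covariate. Even on the generous reading the baseline-adjusted average is stronger.

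The flat profile is also an assumption. The boosters come one and two months after the last in-person session, so a difference that grows after month 1 is possible and would give a non-zero interaction. The conclusion therefore concerns a plausible pattern, not every pattern.

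Choice of contrast is often left to an analysis plan that is not shown here. But the article does not leave it open: it states a test, and that test does not match its hypothesis.

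Three stronger readings are tempting and not supported:

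- **That the trial would yield no adherence effect estimate.** A model with an interaction still gives visit-specific differences, and Participants commits to odds ratios.
- **That a sustained benefit would simply be reported as no difference.** Participants, Quantitative data analysis plan and Hypotheses testing all put estimation and pattern ahead of significance.
- **That the fallback inflates error for the planned test.** The article does not define its general linear model. If visits were stacked as independent rows (ρ = .6, complete data), the false-positive rate for the arm main effect would be about 18.5%; the formula 2[1 − Φ(1.96/√2.2)] gives .19. For the named interaction it would be about 0.1%, which is conservative. The inflation matters only once an arm effect is tested.

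**Conclusion.** The concern holds for MEMS adherence, at moderate weight. As the Effectiveness section reads, the named test addresses change in the arm difference after month 1, while the hypothesis is about its presence. A constant benefit from month 1 would be detected at .05, and this follows from algebra without any assumed correlation. If baseline is a time level, the loss is one of power: about .77 against .97 at d = .6 and ρ = .6. Across ρ = .3 to .7 it is .50 to .88 against .94 to .99. These power figures rest on the assumed correlation, two-sided alpha .05, no dropout and a constant difference.

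A reader might extend the point to all effectiveness outcomes. The text does not support that: the interaction sentence concerns adherence, viral load has its own comparison with baseline, and drug use is said only to be analysed by GEE. Adherence is a secondary outcome, after feasibility and acceptability, which limits the consequence.

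**What to change.** In the Effectiveness section, name as the adherence estimate the LS-DU versus health education difference averaged over months 1, 3 and 6. Take it from the GEE with visit as a factor and baseline MEMS adherence as a prespecified covariate, whether or not the arms differ at baseline. Report it with a 95% confidence interval and the visit-specific differences, on a scale that delivers the promised odds ratio. Keep intervention-by-time as a secondary check on durability. If the authors do intend baseline as a time level for that check, they should say so.

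Replace the fallback: if the GEE does not converge, use an independence working correlation with variance clustered on participant, so that the arm effect is not tested in a model that ignores repeated rows. A small-sample variance correction is optional.

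The cost is a few lines of analysis text, with the same data and no extra visits.
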